# Study protocol of a pilot randomized controlled trial of transcranial direct current stimulation paired with reappraisal training for treatment of cannabis use disorder

**DOI:** 10.1371/journal.pone.0328205

**Published:** 2025-08-28

## Abstract

**Introduction:**

As legalization of cannabis products continues, cannabis use becomes more prevalent, and concerns regarding cannabis use disorder (CUD) rise, improving CUD treatment has become increasingly important. Techniques used to regulate emotions, such as cognitive reappraisal, may help manage cravings for cannabis in individuals with CUD. Transcranial direct current stimulation (tDCS), a noninvasive brain stimulation technique, may improve regulation of emotions and reduce substance use. This study aims to determine whether the addition of tDCS to training in cognitive reappraisal leads to greater reductions in cravings and cannabis use than cognitive reappraisal without active stimulation.

**Methods and analysis:**

This longitudinal between-subjects study will recruit 60 participants who will each be randomly assigned to receive either active or sham tDCS. Participants will undergo 5 sessions, each spaced approximately one week apart. In session, they will receive 20 minutes of (active/sham) 1.5mA anodal stimulation over the right dorsolateral prefrontal cortex while receiving training in cognitive reappraisal. Primary outcomes include changes in cannabis use during the study, changes in electroencephalogram brain activity when viewing cannabis cues, and changes in cannabis craving intensity.

**Discussion:**

The results of this study will inform a full-scale randomized controlled trial designed to assess the effectiveness of this intervention. More broadly, these results will add to the literature on the role of tDCS in enhancing CUD treatment.

**Trial registration:**

ClinicalTrials.gov NCT06369311

## Introduction

As the legalization of cannabis products continues with cannabis use becoming more prevalent, concerns regarding cannabis use disorder (CUD) have been increasing [1]. Concurrently, efforts continue towards improved CUD treatment [2–6]. Craving, a strong desire to use a substance or engage in a behavior, is a defining feature of substance use disorders, including CUD [7]. Craving has been linked to treatment outcomes [8,9], where stronger cravings are typically associated with poorer treatment outcomes [2,10,11].

Since craving may be considered a motivational state that can be regulated [12,13], identifying ways to reduce craving is a common target of evidence-based treatments such as cognitive behavioral therapy and mindfulness-based approaches [3]. One way of regulating craving involves cognitive strategies such as cognitive reappraisal. In the context of CUD, cognitive reappraisal can entail thinking about the negative consequences of engaging in behaviors like using substances [9,12,14–16]. Use of reappraisal strategies in the laboratory has been associated with reduced craving and negative affect among multiple clinical groups, including those who use tobacco [17], cocaine [18], and opioids [4]. Reappraisal training has also been found to be effective for reducing craving for cannabis [5,19] and reducing cannabis use [19–21], making it a promising strategy for enhancing regulation skills, minimizing cravings, and improving treatment outcomes. However, effect sizes tend to be modest. Thus, approaches to enhance reappraisal effects warrant further investigation.

Transcranial direct current stimulation (tDCS), a noninvasive application/administration of electrical current to modulate brain activity and potentially enhance neuroplasticity [22,23], may enhance cognitive reappraisal and craving regulation when applied to the dorsolateral prefrontal cortex (dlPFC). Indeed, the dlPFC has been implicated in regulation of craving [14,24–26]. Preliminary data from clinical research indicates that dlPFC tDCS may be effective in reducing substance use for individuals with alcohol use disorder [27–29], tobacco use disorder [30,31], and CUD, although findings for CUD have been limited by a small sample size (8–9 participants per condition) [6]. Specifically, the CUD study found that participants who received a single session of tDCS to the dlPFC had greater reductions in cannabis craving compared to those who received sham stimulation [6]. Therefore, it is possible that these reductions in craving may be amplified when combining dlPFC-targeted tDCS and training in cognitive reappraisal for CUD.

In addition to its potential to enhance craving regulation, tDCS offers a unique opportunity when paired with electroencephalography (EEG) to explore underlying neurophysiological mechanisms. EEG is a noninvasive, high-temporal-resolution method for measuring brain activity, well-suited for tracking dynamic processes involved in craving and cognitive regulation. Specifically, event-related potentials (ERPs) such as the P300 and late positive potential (LPP) provide sensitive indices of attentional and affective responses to substance-related cues, with increased amplitudes reflecting greater salience or emotional engagement [32–34]. Moreover, frontal theta power, an oscillatory feature associated with cognitive control, has been implicated in the neural implementation of strategies to regulate craving [35]. Integrating EEG into this study may allow for objective assessment of changes in neural features linked to exposure to cannabis-related cues, offering insight into how cognitive reappraisal and tDCS may interact to modulate brain function. Together, the use of EEG and tDCS provides a multimodal framework for both enhancing and monitoring the regulation of cannabis craving in individuals with CUD.

The present study seeks to evaluate the efficacy of tDCS to the right dlPFC paired with training in cognitive reappraisal in improving craving regulation and reducing cannabis use in individuals with CUD. Specifically, we hypothesize that participants who receive active versus sham tDCS will have 1) greater reductions in daily cannabis use, 2) changes in neural correlates of EEG features associated with craving (e.g., relatively diminished LPP amplitude and increased delta power) while viewing cannabis cues, and 3) greater reductions in cannabis craving. We also hypothesize tDCS-related increases in neural correlates of EEG features associated with regulation (e.g., frontal theta power).

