### Primary outcomes

The first primary outcome is cannabis use during the study. This will be measured through a brief daily survey. Participants will be sent a link to a REDCap survey at 8:00am daily to report on cannabis use over the last 24 hours. Participants will be asked about the amount of cannabis used, the form of cannabis used (e.g., smoked, vaped), and how the amount used compares to their typical use amount on a 5-point Likert scale, where 1 indicates much less cannabis used than usual, 3 indicates the usual amount of cannabis was used, and 5 indicates much more cannabis used than usual.

The second primary outcome is the EEG correlates of craving and regulation during the ROC task (Fig 2), which participants will complete before the first intervention session and after the fifth intervention session. The ROC task utilizes E-Prime software to present participants with a series of validated cannabis images, including pictures of the cannabis plant and images depicting various cannabis primary use methods [51]. The ROC task consists of 25 LOOK and 25 NEGATIVE trials total, presented in alternating LOOK and NEGATIVE blocks of 5 trials each (i.e., 5 LOOK trials, followed by 5 NEGATIVE trials, followed by 5 LOOK trials, etc.). During the LOOK trials, participants will be instructed to simply look at the image; during the NEGATIVE trials, participants will be instructed to think about the negative consequences of using cannabis. EEG data will be collected using a 128-lead Electrical Geodesic EEG system, with gel-based collection, sampled at 1000 Hz.

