**Fig 2 pone.0328205.g002:**
[figure not shown]
Schematic representation of a single trial of the ROC task. Participants will view a fixation cross for 3 seconds before the instruction (LOOK/NEGATIVE) for participants is displayed for 3 seconds. A cannabis image will be displayed for 6 seconds, during which participants are to either look at the image (“LOOK”) or think about the negative consequences of using cannabis (“NEGATIVE”). After a 3-second fixation cross, participants will have up to 10 seconds to rate their level of craving for cannabis on a 5-point scale. Participants will complete 50 trials, comprising 25 LOOK trials and 25 NEGATIVE trials.

Our rationale for ERP component selection and labeling is grounded in the literature on emotional image processing. In picture-viewing paradigms involving affectively salient stimuli, the early neural response often overlaps with the P300 in both timing and topography. However, unlike discrete stimuli used in tasks like oddball tasks, emotional images typically evoke more complex and variable cognitive appraisal processes, leading to temporal jitter in the onset of peak neural engagement across trials. This results in a less sharply defined P300 and the emergence of a sustained slow-wave positivity that blends with the LPP over centro-parietal regions. To align with conventions in the ERP literature, we assess the P300 in the ~ 250–300 ms window and the LPP in the 600–900 ms window. Thus, mean amplitudes of the P300 (~250–300 ms following cannabis cue) and the early LPP (600–900 ms following cannabis cue) will be quantified. Additional analysis will also assess and consider frontal theta power.

The third primary outcome is self-reported levels of cannabis craving. This will be assessed using the MCQ [37], which will be administered immediately before and after each tDCS and reappraisal training session at each study visit. It will also be assessed using the ROC task on V1 and V5: self-reported levels of craving in response to cannabis images will be averaged separately across all LOOK trials and all NEGATIVE trials and compared.

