### Data analysis

Data collected throughout this study will primarily be analyzed using SPSS software. To address the first aim of the study, reductions in cannabis use, as reported by research participants through the daily-administered REDCap surveys, will be analyzed using a multilevel modeling strategy. Multilevel modeling with maximum likelihood estimation for missing data will be used to conduct a linear analysis of daily use of cannabis using a nested hierarchical structure with both between- and within-subject predictors. The main effects of Group (i.e., stimulation versus sham) and Time, as well as the Group x Time interaction will be the primary fixed effects of interest. Daily use of cannabis will be compared across the study weeks, and multilevel models will be constructed to examine the slopes of longitudinal data across the weeks.

Statistical analysis of the EEG correlates of craving and regulation will be conducted using Netstation pipelines for ERPs and Matlab scripts for oscillatory power. Data will be filtered offline at 0.1–30 Hz. Ocular artifact correction will be performed on the mean amplitudes of each component with a specified timeframe. The components of interest for this analysis will consist of the P300, the LPP, and frontal theta power. These variables will be compared across Group (i.e., stimulation versus sham), Condition (i.e., LOOK or NEGATIVE), and Time (V1 and V5) in a series of ANOVAs. We hypothesize that active stimulation will result in heightened amplitude of the early LPP in the LATER condition, as regulation of craving is hypothesized to be enhanced, and diminished amplitude of the late LPP in the LATER condition, as arousal related to craving is hypothesized to be reduced. Further, we expect that frontal theta power will be enhanced after tDCS stimulation during the LATER condition.

For the third primary outcome, craving will be measured both pre- and post-tDCS using the MCQ [37], and active and sham groups will be compared via an ANOVA (Group x Condition x Time). Additionally, self-reported cravings elicited by cannabis images in the ROC task in both the LOOK and NEGATIVE conditions are rated on a 5-point Likert scale at baseline and post-treatment. These data will be averaged across trials and compared between groups via an ANOVA (Group x Condition x Time).

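### The LPP is predicted to fall in one section and to rise in another, yet only one LPP window is scored, so a significant change in either direction can be read as support

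*Protocol article*

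**What the plan says.** The Primary outcomes section makes EEG a primary outcome: "The second primary outcome is the EEG correlates of craving and regulation during the ROC task".

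The statements about the LPP are spread over three sections of the protocol article:

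- **Introduction, EEG rationale.** The P300 and LPP are described as indices of response to substance cues, "with increased amplitudes reflecting greater salience or emotional engagement".
- **Introduction, hypotheses.** Among the EEG features tied to craving, active versus sham tDCS is expected to give "relatively diminished LPP amplitude" during viewing of cannabis cues. No time window and no task condition are named.
- **Primary outcomes, text after Fig 2.** The LPP is assigned to 600–900 ms, and then "the early LPP (600–900 ms following cannabis cue) will be quantified". No other LPP window appears.
- **Data analysis.** The prediction is that "active stimulation will result in heightened amplitude of the early LPP in the LATER condition", explained by better regulation, together with "diminished amplitude of the late LPP in the LATER condition", explained by lower craving-related arousal. The components to be analysed are the P300, the LPP (without early or late) and frontal theta. They are compared by Group, Condition (LOOK or NEGATIVE) and Time (V1 and V5) in ANOVAs.

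**The concern.** An ANOVA F test carries no direction. Whether a significant result supports the hypothesis must therefore come from the written prediction. Here the one LPP measure that will exist has a decrease predicted in the Introduction and an increase predicted in Data analysis, each with its own favourable reading. The condition that Data analysis names is not part of the task, so it cannot be used to tell the two predictions apart.

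The trial is meant to inform a full-scale trial. An LPP result that counts as support whichever way it goes cannot tell the designers of that trial whether the proposed mechanism was engaged.

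**Working it through.** The article gives no alpha, effect size or SD for this outcome, so there is no stated figure to reproduce. The check is mainly a comparison of the text.

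**1. The statements side by side**

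| Place | Measure | Predicted change with active tDCS | Condition | Reading given |
|---|---|---|---|---|
| Introduction, hypotheses | LPP, no window | down | none named | craving feature |
| Data analysis | early LPP | up | LATER | better regulation |
| Data analysis | late LPP, no window | down | LATER | less craving arousal |
| Primary outcomes | LPP = early LPP = 600–900 ms | none stated | not applicable | none stated |

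**2. Can the time window separate the predictions?** The Introduction's decrease matches the late-LPP prediction in direction and in rationale, so it may have been meant for the late LPP. But no late window is defined, and the list of components contains only one LPP. The decrease can then be tested only at 600–900 ms, which the article labels early and where Data analysis predicts an increase.

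**3. Can the task condition separate them?** The Introduction speaks of viewing cannabis cues, which covers LOOK and NEGATIVE trials alike. Data analysis puts both its LPP predictions in LATER. Primary outcomes, the Fig 2 legend and the factor list in Data analysis itself all define only LOOK and NEGATIVE. No stated rule assigns one direction to one condition.

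**4. Size of the ambiguity under the null**

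Inputs: 60 participants (Abstract) at 1:1 (Study design), so about 60 / 2 = 30 per arm. Alpha is assumed.

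Group, Condition and Time each have two levels, so each contrast has one numerator degree of freedom and F = t². A significant result at level α then splits evenly between the two directions when there is no effect:

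- one stated direction counts as support: α / 2
- either direction counts as support: α

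| Assumed α | One direction | Either direction |
|---|---|---|
| 0.01 | 0.005 | 0.01 |
| 0.05 | 0.025 | 0.05 |
| 0.10 | 0.05 | 0.10 |

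A simulation of 100,000 null trials (two-sample t test, 30 per arm, α = 0.05) gave 0.026 for one direction and 0.051 for either.

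**The case against.** The strongest defence is that the article holds one two-process hypothesis: an early LPP that rises with regulation and a late LPP that falls with craving arousal. The Introduction's decrease would then simply be the late part. This is a fair reading and may be what was intended. It moves the defect without removing it, because the late part then has a prediction and no measure.

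A second defence is that the two sections may mean different task conditions. The text does not establish that they mean the same one, but it does not establish that they differ either, and LATER cannot settle it.

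A third is that an article condenses a fuller protocol, which may define a late window. That could make the repair easier. The point, however, is not an omission: the article states two directions and applies the labels LPP and early LPP to the same window.

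A reader might also infer several stronger things that the article does not support:

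- *The whole EEG outcome cannot fail.* Frontal theta is predicted to rise in both the Introduction and Data analysis, and a null LPP result would support neither LPP prediction.
- *The false-positive rate of the test is inflated.* It is not. The 2.5% and 5% describe how a result may be read; they are the arithmetic of one tail against two.
- *A harmful effect would be published as benefit.* The Introduction links larger amplitudes to salience or engagement. During NEGATIVE trials, when participants are told to think of bad consequences, more engagement is not clearly harm.
- *The P300 is also defective because it has no predicted direction.* A component tested without a predicted direction is not an error.

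**Conclusion.** The contradiction stands, limited to the LPP component of the second primary outcome. The article predicts a decrease and an increase that, as written, can be tested only on the same 600–900 ms measure, and it ties two of its three LPP predictions to a condition the task does not contain. A significant active–sham difference in either direction can be cited as support. Under the null, the chance of that is 5% rather than 2.5% at an assumed two-sided 5% level, and twice the one-direction figure at any other level. The cannabis-use and craving outcomes are unaffected, and the planned tests would not change.

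Severity: should-fix. The trial is a pilot and EEG is one of three primary outcomes, but the correction is cheap and changes what the LPP result can show.

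**What to change.** Before EEG data are available:

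1. In Data analysis, replace LATER with the task condition meant (LOOK or NEGATIVE), and name the Group × Condition × Time contrast that tests the LPP hypothesis. The frontal theta prediction uses the same label and needs the same correction.
2. Choose one of two routes. Either define a late-LPP window in Primary outcomes, assign the Introduction's decrease to it and keep the increase for 600–900 ms; or drop the late-LPP prediction and state one direction for 600–900 ms, the same in the Introduction and Data analysis.
3. Give one interpretation per window. It should agree with the Introduction's reading of larger amplitudes or state why it departs from it.
4. Keep the test two-sided, and state that a significant change opposite to the prediction does not support the hypothesis.

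Cost: mainly wording. One of the two directions can no longer be claimed as support for a given window. A late window, if added, can be scored from the same EEG recording, since the image stays on screen for 6 seconds. It means a little more scoring and one more test.

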## Materials and methods

### Study design

This protocol is written in accordance with the Standard Protocol Items: Recommendations for Interventional Trials (SPIRIT) reporting template [36]. The present study will utilize a randomized design where participants are allocated to either an active stimulation condition or a sham control condition in a 1:1 ratio. To ensure randomization of active/sham administration across sexes, this 1:1 ratio is allocated within males and females separately. To minimize bias, both study participants and research staff running study visits will be blinded to the participant’s assigned experimental condition. This entails five weekly visits (baseline and four weekly visits thereafter), during which participants will undergo a 20-minute session of (active/sham) tDCS and reappraisal training each week. Participants will complete a self-report measure of cannabis craving [37] immediately before and after each tDCS and reappraisal training session. Before the first tDCS session on the first visit and after the last tDCS session on the fifth visit, participants will complete the Regulation of Craving (ROC) task [3,38], during which EEG activity will be recorded. In addition to the in-person study visits, beginning after the first study visit and ending at the last visit, participants will provide information on past 24-hour cannabis use through a daily survey delivered via short message services (SMS).

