### Participants

#### Eligibility criteria.

Participants will consist of 60 adults between the ages of 18 and 50 years who reside in the Greater New Haven area in Connecticut, USA and meet criteria for moderate or severe CUD. Diagnostic criteria for CUD will be assessed during screening procedures utilizing a symptom checklist based on the Diagnostic and Statistical Manual for Mental Disorders, 5^th^ Edition (DSM-5) criteria for CUD. Participants must meet at least four of these criteria to be eligible for the study. Additionally, participants must be looking to reduce their cannabis use and must have a positive urine toxicology screen for metabolites indicating regular cannabis use. Participants must also have the capacity to provide informed consent for the study.

Participants may be excluded from the study for several reasons. First, participants may not be receiving any other form of treatment for CUD while they are participating. Lifetime history of serious neurological (e.g., dementia, multiple sclerosis, tumors) or psychiatric (e.g., psychosis, bipolar disorder) conditions, strokes, or losses of consciousness will preclude participants from being eligible. Participants will also be excluded if they have a current medical history of non-CUD substance use disorders. Several contraindications to tDCS will also prevent participants from safely participating, including the presence of metallic implants or electronic devices (e.g., heart pacemakers), any history of seizures, and pregnancy or a plan to become pregnant during the duration of the study. Finally, participants will be excluded for endorsing suicidal or homicidal thoughts, using nicotine equivalent to one pack of cigarettes per day or more, or using exclusionary substances, including amphetamines, benzodiazepines, methamphetamine, cocaine, and opioids. Participants who primarily use cannabis in the form of edibles will be excluded, as the ROC task for CUD utilizes cannabis images related to smoking and vaping and does not include pictures of edibles.

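### Randomisation is stratified by sex but no stated analysis names sex; if sex is prognostic, standard errors will be somewhat too wide and tests conservative

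*Protocol article*

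**What the plan says.** Under Study design, "participants are allocated to either an active stimulation condition or a sham control condition in a 1:1 ratio", and the article adds that "this 1:1 ratio is allocated within males and females separately". Sex is therefore a stratification factor with two levels. Block size, or any other means of holding the ratio within each sex, is not given. The Baseline measures section records sex on the demographics form.

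The Data analysis section describes four analyses:

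- **Daily cannabis use.** A multilevel model "using a nested hierarchical structure with both between- and within-subject predictors". The main effects of Group and Time, "as well as the Group x Time interaction will be the primary fixed effects of interest".
- **EEG measures.** Comparison across Group, "Condition (i.e., LOOK or NEGATIVE), and Time (V1 and V5) in a series of ANOVAs".
- **MCQ craving.** The "active and sham groups will be compared via an ANOVA (Group x Condition x Time" being the listed factors.
- **ROC craving ratings.** These are "compared between groups via an ANOVA (Group x Condition x Time" again being the listed factors.

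Sex is named in none of the four. The three ANOVAs are given as factor lists without it. The daily-use text names only the effects of interest and leaves the other predictors open.

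**The concern.** Stratified allocation forces the arms to have nearly the same sex mix. Any outcome difference between men and women then contributes almost nothing to the difference between arms. A model without sex does not know this: it counts the sex difference as ordinary residual variation and reports a standard error that allows for imbalance the design has prevented. Confidence intervals come out too wide and tests reject too rarely.

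With 60 participants, precision is scarce. The Abstract says the results will inform a full-scale trial, so an overstated error term could also pass into its planning.

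**Working it through.** **Inputs from the article.** N = 60 ("Participants will consist of 60 adults between the ages of 18 and 50 years"), allocated 1:1, so about 30 per arm, with two sex strata. The article states no alpha, power, standard deviation or sex effect, so there is no figure of the plan's own to reproduce.

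**Assumptions.** Two-sided 5% test; exact balance within sex; R² = share of the analysed variance explained by sex, taken as 0 to 20%.

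**Formula.** With total variance σ² and equal arms, the model without sex reports SE = √(4σ²/N). With arms balanced within sex, the true value is √(4σ²(1 − R²)/N). The ratio is 1/√(1 − R²). The actual type I error is 2 × [1 − Φ(1.96/√(1 − R²))]. A test with 80% power when adjusted (shift 1.96 + 0.84 = 2.80) has unadjusted power Φ(2.80 − 1.96/√(1 − R²)).

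| R² (assumed) | SE ratio | Actual type I error | Power if 80% when adjusted |
|---|---|---|---|
| 0 | 1.000 | 5.0% | 80.0% |
| 1% | 1.005 | 4.9% | 79.7% |
| 5% | 1.026 | 4.4% | 78.5% |
| 10% | 1.054 | 3.9% | 76.9% |
| 20% | 1.118 | 2.8% | 72.9% |

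**Which variance R² refers to.** The Group main effect compares person means, so R² is the share of between-person level that sex explains. Group x Time compares within-person changes. Subtracting a person's early value from the late one removes anything constant for that person, including a sex difference in level. For that test, R² is the share of the *change* that sex explains. For Group x Condition x Time it is the share of the corresponding change contrast.

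**Simulation check.** 6,000 trials per scenario, N = 60, two time points; 60% male and a within-person correlation of 0.6 are assumed. In these units the person mean has variance 0.6 + 0.4/2 = 0.8 and the change 2 × 0.4 = 0.8 before any sex effect. The true SE should therefore be √(4 × 0.8/60) = 0.231. With R² = 20% the total variance is 0.8/0.8 = 1.0, and the unadjusted SE should be √(4/60) = 0.258.

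| Allocation | Sex effect | Test | Unadjusted SE / true SD | Type I error | With sex in the model: SE, type I error |
|---|---|---|---|---|---|
| Balanced within sex | None | Group | 0.230 / 0.230 | 4.7% | 0.230, 4.7% |
| Balanced within sex | 20% of level | Group | 0.259 / 0.230 | 2.8% | 0.230, 4.7% |
| Balanced within sex | 20% of level | Group x Time | 0.230 / 0.229 | 4.9% | 0.230, 4.9% |
| Balanced within sex | 20% of change | Group x Time | 0.258 / 0.231 | 2.9% | 0.230, 4.7% |
| Unrestricted | 20% of level | Group | 0.260 / 0.257 | 4.8% | 0.234, 4.6% |

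In the Group x Time rows the test is on the change score, so putting sex in that model is the same as adding Sex x Time. The simulation agrees with the formula. It also shows the two conditions: the excess width disappears if sex is unrelated to the quantity tested, or if allocation is not really balanced within sex.

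**The case against.** The strongest reply has four parts.

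1. **Nothing shows that sex is prognostic, or how balance is enforced.** This stands. A reader might infer that the reported standard errors *will* be too wide; the article does not support that. It gives no association between sex and any outcome and no blocking scheme. Its wording shows that balance within sex is intended, but not how closely it will be achieved.

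2. **The hypotheses on use and craving concern reductions, from which a sex difference in level cancels.** This stands for the interaction tests. It does not dispose of the point, because the Data analysis section also lists the main effect of Group among the primary fixed effects of interest for daily use. The daily surveys start only after the first visit, at which the first stimulation session is given. That series has no pre-treatment daily value, so comparisons of level between arms carry weight.

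3. **Covariates are commonly settled in the analysis plan, which is not shown.** This stands for daily use: the text leaves other predictors open, and it would be wrong to read it as excluding sex. It has less force for the three ANOVAs, whose factors are written out and do not match the randomisation.

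4. **The error is on the safe side.** This stands. False positives are not inflated, and the trial is a pilot.

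**Conclusion.** The point holds in conditional form and is minor. The randomisation uses sex; the ANOVAs as written do not, and the daily-use model does not name it. If sex is prognostic for the quantity tested and arms are balanced within sex, standard errors are overstated by 2.6% to 11.8% for an assumed R² of 5% to 20%. A test with 80% power when adjusted would then have 78.5% to 72.9%. At R² = 1% the overstatement is 0.5%.

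The mismatch between design and analysis is certain; the size of its effect is not, since every R² here is an assumption. Two stronger readings are not supported. The same inflation cannot be applied to Group x Time on the strength of a sex difference in level, because only a sex difference in change matters there. Nor does the omission make any effect estimate wrong.

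**What to change.** Add sex, in the form used for the randomisation, to every primary model, with its interactions with the within-person factors being tested:

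- **Daily-use multilevel model:** Sex and Sex x Time.
- **MCQ, ROC craving and EEG ANOVAs:** sex as a between-subject factor, crossed with Time and Condition but not with Group. The between-subject part should be specified explicitly as Group plus Sex, so that a full-factorial default does not add Group x Sex.

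A sex main effect alone would be enough for the Group main effect but would leave the interaction tests unchanged. If the analysis plan already includes these terms, the article need only say so; if sex is left out on purpose, it should state why. One sentence on how the ratio is held within each sex would also help.

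The cost is small. Sex is already collected. For a between-person contrast in 60 participants the residual degrees of freedom go from 60 − 2 = 58 to 60 − 3 = 57, so about one is lost per tested contrast if sex proves unrelated to the outcome.
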